### Endpoints

#### Primary endpoints

The primary endpoints of this study include DGF during one week post transplantation, and biopsy proven acute rejection (BPAR) over one year.

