### Sample size

The sample size was calculated based on our previous data showing that there was no BPAR in the MSC treatment group at 6 months after transplantation, compared with 16.7% of acute rejection in the control group [21]. Based on this preliminary study, we calculated that 44 patients per arm will be required to achieve power of 90% with a two-sided significance level of *P* < 0.05. To account for possible dropouts (10%), the target number of patients was, therefore, set at 50 per arm (100 in total) (see Additional file 1).

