### Statistical analysis

Parametric (e.g., analysis of variance (ANOVA)) and non-parametric (e.g., Kruskal-Wallis test) statistical tests will be applied using the SPSS version 21 (SPSS Inc., Chicago, IL, USA) for the data analysis. Multi-level regression analysis will be used to examine differences between trial arms for the endpoints. The logistic model will be applied for binary endpoints, and linear regression will be for continuous endpoints. All analyses will follow intention-to-treat principles and a pre-specified analysis plan. As for missing data values, we will apply mean imputation and regression imputation where rates are low, and consider multiple imputations where they exceed 10%. Since multiple tests are performed simultaneously, the Bonferroni correction will be made during analysis to determine the critical *P* value for significance. *P* values < 0.05 will be considered as statistically significant. The SPIRIT checklist is provided in Additional file 2.

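### Power for BPAR is stated at an unsplit two-sided 0.05, while the analysis section sets the critical P value by Bonferroni; the two levels need to be aligned

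*Protocol article*

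**What the plan says.** Three places in the protocol article bear on the level at which BPAR is tested.

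- **Primary endpoints.** There are two: "The primary endpoints of this study include DGF during one week post transplantation, and biopsy proven acute rejection (BPAR) over one year".
- **Sample size.** The calculation uses BPAR only. The pilot rates are given as "there was no BPAR in the MSC treatment group at 6 months after transplantation", "compared with 16.7% of acute rejection in the control group". From these, "44 patients per arm will be required to achieve power of 90% with a two-sided significance level of" 0.05. Allowing for 10% dropout, the target is 50 per arm. The section mentions neither a second primary endpoint nor a correction.
- **Statistical analysis.** "Since multiple tests are performed simultaneously, the Bonferroni correction will be made during analysis to determine the critical" P value. The number of tests is not given and no endpoint is exempted. The next sentence says that P values below 0.05 count as significant. Binary endpoints are to be analysed with a logistic model.

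**The concern.** A Bonferroni-determined critical value lies below 0.05 for any family of two or more tests. A power figure computed at the full 0.05 is then not the power of the test that the analysis section announces. If BPAR turns out non-significant, readers will judge that result against 90%. They would be relying on a figure calculated for a more lenient test than the one performed.

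This is separate from whether 44 per arm is the right number at 0.05. Any sample size fixed at 0.05 loses power when the test is run at a stricter level.

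**Working it through.** **Inputs.** From the Sample size section: control rate p = 0.167, treated rate 0, n = 44 evaluable per arm (50 enrolled), two-sided 0.05. Number of tests: not stated. I take m = 2, the two primary endpoints, so α = 0.05/2 = 0.025. A larger family gives a smaller level.

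**Pooled normal approximation.** With the average rate p̄ = 0.0835,

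z = [p√n − z(1−α/2)·√(2p̄(1−p̄))] / √(p(1−p)), and power = Φ(z).

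Here √(2 × 0.0835 × 0.9165) = 0.3912 and √(0.167 × 0.833) = 0.3730.

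- n = 44, α = 0.05 (the plan's own setting): (1.1078 − 1.960 × 0.3912)/0.3730 = 0.914, power 82%.
- n = 44, α = 0.025: (1.1078 − 2.241 × 0.3912)/0.3730 = 0.619, power 73%.
- n = 50, α = 0.05: z = 1.110, power 87%.
- n = 50, α = 0.025: z = 0.815, power 79%.

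The plan's 90% is not reproduced at its own setting. That is a different question, and the gap from 90% to 82% is not counted here.

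**Exact power.** With a true rate of 0 the treated arm has no events, so power is the chance that the control arm reaches the smallest count c that gives significance, with X ~ Binomial(n, 0.167). At n = 44:

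| Test | c at 0.05 | Power | c at 0.025 | Power |
|---|---|---|---|---|
| Fisher's exact | 6 | 77% | 7 | 62% |
| Uncorrected chi-square | 4 | 95% | 5 | 88% |
| Likelihood-ratio (single-level logistic, no site effect) | 3 | 98.5% | 4 | 95% |

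Under each test the stricter level demands exactly one more control-arm rejection. At n = 50 the figures are 86% and 75% (Fisher), 98% and 94% (chi-square), and 99% and 98% (likelihood-ratio).

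**Loss due to the level alone at n = 44.** Pooled: 82.0 − 73.2 = 8.8 points. Fisher: 76.6 − 61.8 = 14.8. Chi-square: 95.0 − 87.9 = 7.1. Likelihood-ratio: 98.5 − 95.0 = 3.5.

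**Independence from the size of n.** By the pooled formula, 90% power needs 56 per arm at 0.05 and 66 at 0.025. A trial sized at 56 would have 84% at 0.025, so correcting n at 0.05 would not remove the mismatch.

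**Larger families** (pooled, n = 44): m = 3 gives 68%, m = 4 gives 64%, m = 5 gives 61%.

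**The case against.** Four objections deserve an answer.

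1. *The analysis section also keeps P < 0.05.* This makes the text ambiguous. If it refers to Bonferroni-adjusted P values, the level for a raw P value is still 0.025 or less and the mismatch stands. If it refers to unadjusted P values, it contradicts the preceding sentence. A reader might infer that the protocol tests BPAR at 0.025; it does not say so. That figure is an assumption about an undefined family.

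2. *The analysis plan and the additional file are not shown, and may define the family.* Leaving the family to the analysis plan is normal and is not criticised here. But no family of two or more that contains BPAR brings its level back to 0.05. Only an exemption for BPAR would, and the article gives none.

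3. *The power of the planned test has not been shown to fall below 90%.* This stands. The plan names a multi-level logistic model, and with no events in one arm the result depends heavily on the test: from 62% to 95% at 0.025 with 44 per arm. A likelihood-ratio test would stay above 90%. It and the uncorrected chi-square can be anti-conservative with sparse events, and a Wald test breaks down with a zero cell; the article does not say which version is used. What survives is that power is lower at 0.025 than at 0.05 under every test examined.

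4. *The Discussion already concedes that the trial may be underpowered.* That is a general caution. It does not correct the 90% or mention the level.

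**Conclusion.** The point holds as an inconsistency of significance level: the sizing uses an unsplit two-sided 0.05, and the analysis announces a Bonferroni-determined critical value with two primary endpoints. Assuming a family of two and the plan's own rates, the mismatch alone costs about 9 points of power at 44 per arm by the pooled approximation, 15 by Fisher, 7 by uncorrected chi-square and 3 to 4 by the likelihood-ratio test.

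Two stronger conclusions that a reader might draw are not supported. One is that the planned test has only 73% power: neither the family nor the form of the logistic test is given, and some forms exceed 90% even at 0.025. The other is that the whole fall from 90% to 73% comes from Bonferroni: by the pooled formula, 8 of those 17 points arise already at 0.05. Type I error is not at risk if the correction is applied as announced; what is wrong is the stated power.

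**What to change.** State once the level at which BPAR is tested, and make the Sample size and Statistical analysis sections agree. Either route works:

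- **Keep BPAR in the Bonferroni family.** Restate the power at that level and name the test. For example: *BPAR is tested at two-sided 0.025 (Bonferroni over the two primary endpoints); for 0% versus 16.7%, 44 evaluable patients per arm give about 73% power and 50 give about 79% (pooled two-proportion z-test).* If another test is to be used, give its figure instead.
- **Test BPAR at the full 0.05.** Say in the Statistical analysis section that BPAR lies outside the Bonferroni family, and state how error is controlled for DGF.

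In both cases, say whether the 0.05 threshold in the Statistical analysis section applies to adjusted P values.

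The cost is a sentence or two. No extra patients and no change in conduct are needed. The first route makes the stated power less favourable; the second needs an explicit account of error control across the two primary endpoints.

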### Statistical analysis

Parametric (e.g., analysis of variance (ANOVA)) and non-parametric (e.g., Kruskal-Wallis test) statistical tests will be applied using the SPSS version 21 (SPSS Inc., Chicago, IL, USA) for the data analysis. Multi-level regression analysis will be used to examine differences between trial arms for the endpoints. The logistic model will be applied for binary endpoints, and linear regression will be for continuous endpoints. All analyses will follow intention-to-treat principles and a pre-specified analysis plan. As for missing data values, we will apply mean imputation and regression imputation where rates are low, and consider multiple imputations where they exceed 10%. Since multiple tests are performed simultaneously, the Bonferroni correction will be made during analysis to determine the critical *P* value for significance. *P* values < 0.05 will be considered as statistically significant. The SPIRIT checklist is provided in Additional file 2.

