### Study design

This is a prospective multicenter controlled study including three kidney transplant institutions (the third affiliated hospital of Sun Yat-sen University, Zhujiang hospital of Southern Medical University, and the second affiliated hospital of Guangzhou Traditional Chinese Medicine University). The protocol has been approved by the Ethics Committee of Human Study at the three institutions, which were established according to the Operational Guidelines for Ethics Committees that Review Biomedical Research developed by the World Health Organization (WHO) [22].

No organs from executed prisoners will be used in the study, and procurement of kidneys from all donors will be conducted in accordance with the WHO principles, Declaration of Helsinki and Istanbul declaration [23, 24]. Organ donation and recovery will be conducted by organ procurement organizations in the three kidney transplant institutions, which were established by the National Health and Family Planning Commission of China. Before procurement, written consent will be obtained from the donor’s immediate family, agreeing to donation of the kidney and withdrawal of life support. The obtained consent for donation will be then reported to the Organ Donation Committee, which supervises the donation process.

All the participants in this study will provide informed, written consent to undergo this study. Participants receiving renal transplantation with deceased-donor grafts will be recruited and randomly divided into two groups. The trial group will undergo peripheral vein injection of human UC-MSCs in the 48 hours before the operation, and renal arterial injection during the operation. The control group will not receive UC-MSC treatment. All the participants will have standard induction therapy. All the participants will be recruited from the three transplant units and meet the eligible criteria. The Standard Protocol Items: Recommendations for Interventional Trials (SPIRIT) Figure is provided in Fig. 1.

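### The trial is sized on no BPAR events in the UC-MSC arm, but the logistic model named for BPAR has no finite odds ratio and no usable Wald inference when an arm has no events

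*Protocol article*

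**What the plan says.** The Endpoints section makes BPAR over one year one of two primary endpoints. The Sample size section takes its rates from the group's own earlier data, in which "there was no BPAR in the MSC treatment group at 6 months after transplantation", "compared with 16.7% of acute rejection in the control group". From these it derives 44 patients per arm for 90% power at two-sided 0.05, raised to 50 per arm for 10% dropout.

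The Statistical analysis section fixes the comparison of arms: "Multi-level regression analysis will be used to examine differences between trial arms for the endpoints". For endpoints such as BPAR it adds: "The logistic model will be applied for binary endpoints". It does not say whether inference will use a Wald, likelihood-ratio or other test. It gives no alternative for an arm without events. It refers to a pre-specified analysis plan, which is not shown, and says that a Bonferroni correction will be made.

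**The concern.** The two sections do not fit together. The planning scenario puts no events in one arm, and the named model cannot give a finite treatment effect from such data. Standard output would then show a very large negative coefficient, a very large standard error and a Wald P near 1, even though the data favour UC-MSCs clearly.

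The risk is that a primary result depends on a choice made after the data are seen. On identical data, the unstated choice of test moves the P value from near 1 to below 0.001. If the analyst switches method at that point, the result no longer comes from a pre-specified analysis, and readers may fairly discount it.

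**Working it through.** **Inputs.** From Sample size: UC-MSC rate 0% (at 6 months), control rate 16.7%, 44 per arm before and 50 after dropout, two-sided 0.05, power 90%. Assumed here: true one-year UC-MSC rates of 1%, 2%, 3% and 5% as a range around zero. All calculations compare two arms and ignore centre.

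**The plan's own figure.** The pooled normal formula is n = [z₀.₉₇₅√(2p̄(1−p̄)) + z₀.₉₀√(p₁(1−p₁) + p₂(1−p₂))]² / (p₁−p₂)². With p₁ = 0.167, p₂ = 0 and p̄ = 0.0835 it gives 55.6, so 56 per arm. The unpooled form gives 53 and Fisher's exact test 54. The stated 44 is not reproduced at two-sided 0.05 and 90%; that is a separate matter. The dropout step is consistent: 44/0.9 = 48.9, and the target is 50.

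**Why the estimate diverges.** Expected control events are 50 × 0.167 = 8.35, so take 0/50 against 8/50. Every UC-MSC patient is a non-event, so the likelihood keeps rising as the treatment coefficient falls and has no finite maximum. A random effect does not change this, because the same holds at any value of the random effect. An iterative fit gives:

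| Iterations | Log OR | SE | Wald P |
|---|---|---|---|
| 10 | −9.9 | 28 | 0.72 |
| 20 | −19.9 | 4134 | 0.996 |
| 30 | −29.9 | 6.1 × 10⁵ | 1.000 |

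These values depend only on where the fit stops. They are not estimates of anything in the trial.

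**Other methods on the same 0/50 against 8/50:**
- Fisher's exact P = 0.0058
- score (uncorrected chi-square) P = 0.0032
- likelihood-ratio P = 0.0006
- Firth-penalised likelihood-ratio P = 0.0023. In this two-arm case the Firth odds ratio adds one half to each cell: the odds are 0.5 ÷ 50.5 = 0.0099 with UC-MSCs and 8.5 ÷ 42.5 = 0.2 in controls, a ratio of 0.05.

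A Wald test after adding one half to each cell has SE = √2.16 = 1.47, where 2.16 is the sum of the reciprocals of the four cells (0.5, 50.5, 8.5 and 42.5). The log odds ratio is −3.01, so z = −3.01 ÷ 1.47, about −2.04, and P = 0.041. The penalised fit therefore needs to be paired with a likelihood-ratio test.

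**Power at 50 per arm, two-sided 0.05.** Power = Σₓ Σᵧ b(x; 50, 0.167) b(y; 50, p) × 1[P(x,y) < 0.05], where b is the binomial probability. Zero-event data count as not significant for Wald. P(no UC-MSC events) = (1−p)⁵⁰.

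| True UC-MSC rate | P(no events) | Wald | Fisher | Score | Likelihood ratio |
|---|---|---|---|---|---|
| 0% | 100% | 0% | 86.3% | 97.6% | 99.4% |
| 1% | 60.5% | 22.6% | 73.5% | 87.1% | 91.5% |
| 2% | 36.4% | 33.4% | 61.4% | 77.1% | 81.8% |
| 3% | 21.8% | 37.1% | 50.5% | 67.3% | 71.4% |
| 5% | 7.7% | 33.5% | 32.9% | 49.0% | 51.4% |

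At 1%, Wald power cannot exceed 100 − 60.5 = 39.5%, because empty-arm data never reject. At 5% every method has lost power because the effect is smaller, and Wald is then level with Fisher. The shortfall specific to Wald lies at rates near zero.

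**Power of candidate methods at 0% against 16.7%, 44 / 50 per arm.** At 0.05: Fisher 76.6% / 86.3%, score 95.0% / 97.6%, Firth likelihood ratio 95.0% / 97.6%. If Bonferroni means 0.025 for each of two primary endpoints (an assumption): Fisher 61.8% / 75.1%, Firth likelihood ratio 87.9% / 93.6%.

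**The case against.** The strongest reply is that the protocol never names the Wald test. A reader might infer that the stated analysis has no power, and the text does not support that. The likelihood-ratio test of the same simple logistic model has 98.5% power at 44 and 99.4% at 50 per arm. For 0/50 against 8/50 its profile interval for the odds ratio runs from 0 to 0.24. So the model can still give a test and an upper bound, and what fails is the finite estimate and anything based on its standard error. This objection stands and limits the point.

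Second, a reader might infer that an empty arm is certain. It is certain only if the true rate is exactly zero. The zero is a 6-month pilot result, while the endpoint runs one year with protocol biopsies at 14 days and 12 months, and the Discussion speaks of low incidence. This also stands: at an assumed 5% an empty arm has a chance of 7.7%.

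Third, the choice of test and a sparse-data fallback are details often left to an analysis plan, and that plan may cover them. This stands in part. The point here is the mismatch between a model that the article names and the planning rates that it states, not missing detail.

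Fourth, one might infer that the levels of the model are the three centres and criticise a variance resting on three units. The article does not say what the levels are, so that criticism is not made here.

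**Conclusion.** The point holds in a limited form. Under the protocol's own planning rates, the logistic model named for a primary endpoint has no finite treatment estimate, and a Wald P value or interval from it is uninformative. If the Wald test were used, power at 50 per arm would be 0% at a true UC-MSC rate of 0%, and between 22.6% and 37.1% at assumed rates of 1% to 5%, against the 90% claimed. If the likelihood-ratio test were used, power at 0% would be about 99%. The document does not settle which applies.

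This rests on a control rate of 16.7%, two arms without centre, and two-sided 0.05. It says nothing against logistic regression for DGF, and the zero cell gives no reason to change that model.

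**What to change.** In the Statistical analysis section, replace the multi-level logistic model for BPAR by one method that is defined with a zero cell, chosen before the data are seen. Two options:

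- Firth-penalised logistic regression with a penalised likelihood-ratio test and a profile-likelihood interval. Do not pair it with a Wald test.
- An exact or score test with a score interval for the risk difference.

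Then state power for that same method at the significance level left after the Bonferroni correction. The choice matters: at 0% against 16.7% and two-sided 0.05, Fisher's exact test needs 54 per arm for 90% power (61 at 0.025), while the Firth likelihood-ratio test has 97.6% at 50 per arm (93.6% at 0.025).

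The cost is a few lines of plan text and possibly a software procedure other than the one named. If the unseen analysis plan already names such a method, it is enough to align the protocol wording and the power statement with it.

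### The primary significance threshold is left ambiguous after a Bonferroni commitment, and the stated 90% power is for BPAR alone at an undivided 0.05

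*Protocol article*

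**What the plan says.** Primary endpoints section: "The primary endpoints of this study include DGF during one week post transplantation, and biopsy proven acute rejection (BPAR) over one year". There are two, and neither is ranked above the other.

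Statistical analysis section: because several tests are run together, "the Bonferroni correction will be made during analysis to determine the critical" P value for significance. Neither the tests in the family nor the divisor is named. The next sentence says that P "values < 0.05 will be considered as statistically significant". It does not say that these are adjusted P values or that 0.05 is the overall level.

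Sample size section: the planning rates are no BPAR in the cell-therapy arm at 6 months and 16.7% acute rejection in the control arm. From these, "44 patients per arm will be required to achieve power of 90% with a two-sided significance level" of P < 0.05. A 10% dropout allowance brings the target to 50 per arm, 100 in total. The section gives no DGF rate and no divided significance level.

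**The concern.** Two consecutive sentences can be read as different decision rules for the primary endpoints. If the family is the two primary endpoints, a P value between 0.025 and 0.05 counts as positive under an unadjusted 0.05 and may count as negative under Bonferroni.

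This zone is a realistic outcome under the plan's own rates. The expected number of control events among 44 is 44 × 0.167 ≈ 7.3. A result of 0/44 versus 6/44 gives a two-sided Fisher P of 0.026.

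Whichever reading is meant, the power figure was computed at the undivided level, for one of the two endpoints. If 0.05 were applied to each endpoint, the error control that the Bonferroni sentence promises would be lost. If 0.025 is applied, the power is lower than the same calculation gives at 0.05, and the protocol does not say by how much.

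**Working it through.** **Inputs (protocol).** Two primary endpoints; BPAR 16.7% versus 0%; two-sided 0.05; power 90%; 1:1 allocation; 44 evaluable per arm; 10% dropout. **Assumption:** the Bonferroni family is the two primary endpoints, so each level is 0.05/2 = 0.025. This is the smallest natural family; a larger one would lower the level and the power further.

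**1. The plan's own figure.** Pooled formula: n = [z(1−α/2)·√(2·p̄·q̄) + z(1−β)·√(p₁q₁ + p₂q₂)]² / (p₁ − p₂)².
- p̄ = 0.0835, so √(2 × 0.0835 × 0.9165) = 0.3912.
- √(0.167 × 0.833 + 0) = 0.3730.
- At 0.05: (1.960 × 0.3912 + 1.2816 × 0.3730)² / 0.167² = 55.6, so 56 per arm.

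The stated 44 is not reproduced. Exact Fisher needs 54 and an uncorrected Pearson test, enumerated exactly, needs 39. The dropout step is consistent: 44/0.9 = 48.9, rounded up to 50. Because 44 does not reproduce, the cost of the alpha split has to be measured from the power that 44 per arm actually gives at 0.05, not from 90%.

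**2. BPAR power at 44 per arm, before and after the split.**

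Pooled formula: power = Φ[(0.167·√44 − z(1−α/2) × 0.3912) / 0.3730].
- α = 0.05: (1.1078 − 0.7668)/0.3730 = 0.914, giving 82.0%.
- α = 0.025: (1.1078 − 0.8769)/0.3730 = 0.619, giving 73.2%.

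For the exact calculations, the treated arm has 0 events by assumption, so power is the probability that the control count X ~ Bin(44, 0.167) reaches the smallest significant value.
- Fisher: 6 events give P = 0.026 and 7 give P = 0.012. Power is P(X ≥ 6) = 76.6% at 0.05 and P(X ≥ 7) = 61.8% at 0.025.
- Pearson: 4 events give z = 2.05 and 5 give z = 2.30, against critical values of 1.96 and 2.24. Power is P(X ≥ 4) = 95.0% at 0.05 and P(X ≥ 5) = 87.9% at 0.025.

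| Method, 44 per arm | α = 0.05 | α = 0.025 | Loss from the split |
|---|---|---|---|
| Pooled formula | 82% | 73% | 9 points |
| Fisher exact | 77% | 62% | 15 points |
| Pearson, uncorrected | 95% | 88% | 7 points |

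**3. Size for 90% power.** The pooled formula at 0.025 gives (2.2414 × 0.3912 + 1.2816 × 0.3730)² / 0.167² = 65.8, so 66 per arm. Of the step from 44 to 66, the part from 56 to 66 is due to the split; the part from 44 to 56 is the separate reproduction problem.

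**4. Family-wise error.** With each of two tests at 0.05: 1 − 0.95² = 9.75% under independence, with a general bound of 0.05 + 0.05 = 10%. With each at 0.025: 1 − 0.975² = 4.94%.

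**5. DGF (illustration only).** The protocol gives no DGF rate, so control rates of 20%, 30% and 40% are assumed here, each halved by treatment, with the pooled formula and 44 per arm throughout. Power at 0.05 is 26%, 39% and 54%; at 0.025 it is 17%, 29% and 42%.

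**The case against.** **The 0.05 may be the overall level.** A reader might infer that the two sentences flatly contradict each other. The documents do not support that. Under an ordinary reading, 0.05 is the family-wise level that Bonferroni divides, or the threshold for adjusted P values. The protocol does commit to multiplicity control. What stands is that the text does not say which is meant, and that either reading leaves the Sample size section at the undivided level.

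**The gap from 90% is not all due to Bonferroni.** A reader might set 73% or 62% against the stated 90% and charge the difference to the correction. At 0.05 the same methods already give 82% and 77%, so part of that gap is a separate sample-size error. Under Pearson, power at 0.05 exceeds 90%, and with all 50 per arm evaluable it is still 94% at 0.025. None of the three methods is the planned multi-level logistic model.

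**Success might require both endpoints.** The objective speaks of preventing both DGF and rejection. If a positive trial needed both to be significant, each could be tested at 0.05 without inflation. The protocol states no such rule, and it chooses Bonferroni.

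**Dependence.** The 9.75% is not a maximum. The Background links both outcomes to prolonged ischemia, so positive dependence and a lower value are plausible.

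**Other documents.** A pre-specified analysis plan and an additional file on sample size are cited but not shown. The family and divisor may properly be given there, so their absence here is not the point. The Discussion also concedes possible underpowering, without a figure. Neither changes the level at which the article itself states its 90%.

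**Conclusion.** The point holds in a limited form. The protocol commits to a corrected critical value, follows it with an unlabelled 0.05, and reports power for one of two primary endpoints at a level that its own correction rules out.

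With the family taken as DGF and BPAR, the split costs BPAR about 7 to 15 points of power at 44 per arm, depending on the test. This rests on the plan's rates of 0% and 16.7%. The further shortfall from 90% under the pooled formula and Fisher should be handled as a separate matter. The inflation to 9.75% would arise only if the Bonferroni sentence were not applied. DGF power cannot be derived from the document, so the DGF figures above show no error in it; they show only why a planning figure is needed.

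**What to change.** - State that 0.05 is the two-sided family-wise level for a family of two tests, DGF and 12-month BPAR, and remove the blanket P < 0.05 rule for these endpoints.
- Test the pair by Holm: the smaller P value at 0.025 and, if that is significant, the other at 0.05. Bonferroni would also be valid. Holm gives the same error control and is never less powerful.
- Claim prevention of both outcomes only if both hypotheses are rejected.
- Restate BPAR power at 0.025 for the planned size, naming the test.
- Give the detectable DGF difference at the same level, with the control rate labelled as an assumption and one method and one denominator used throughout.

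The cost is wording plus a recalculation, and the stated power becomes less favourable. No added patients are needed. The article reports that recruitment was still open at submission; the rule should be fixed before outcome data are analysed.
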